### Statistical methods

The analysis will consist of three stages. First, we will assess characteristics of the clinics, men receiving HIV care, and the subgroup of OHTN Cohort Study participants at baseline. Second, we will conduct interim preliminary analysis for assessment of the intervention effect and temporal trends at month 18. Finally, we will conduct comparisons between control and intervention periods using intention-to-treat principles at the end of the study period (month 30), once all clinics have had at least one 6-month intervention period.

Outcomes will be summarized across sites for each time period and between control and intervention time periods within sites. We will use tabular and graphical summaries to describe demographic, behavioral, and clinical characteristics of the participants within and across sites and over time. We will check for delayed treatment effects to evaluate the assumption that the 6-month time periods are long enough to see the full intervention effect.

We will estimate the intervention effect using general linear mixed models (Table 1). Models will take into account within and between site variance components, within-subject correlation, and will have random site effects, a fixed time effect and a fixed effect due to the intervention. With only four clinics in the trial, there may be differences in clinic populations that may confound the intervention effect. Therefore, patient-level covariates will be added to the model (i.e., baseline age, viral load, and syphilis test histories) if necessary to adjust for measurable differences in patient populations across clinics and time periods. In the sub-analysis among men receiving HIV care who are participants of the OHTN Cohort Study, we will additionally include covariates such as sociodemographic characteristics and sexual behaviors if these are empirical confounders of the intervention effect. To determine whether the intervention effects on screening coverage and frequency are equivalent among men across sexual behavior characteristics, we will test for statistical interactions between the fixed effect due to the intervention and sexual behavior variables.

**Table 1 Tab1:** Variables, measures, and methods of analysis for ESSAHM trial

Variable/outcome	Hypothesis	Outcome measure	Methods of analysis
1) Primary: syphilis case detection	75 % increase over baseline rate	New, previously untreated syphilis case as a binary measure	GLMM models using SAS PROC GLIMMIX with logit function
2) Secondary: a. screening coverage	Increase to 85 % of men testing annually	Tested one or more times in 6-month study period as a binary measure	GLMM models using SAS PROC GLIMMIX with logit function Compare proportion tested and modify to annualized rates
b. screening frequency	Increase to median of 3 tests per person/year	Number of tests per year as Poisson count outcome data	GLMM models using SAS PROC GLIMMIX with log link function
c. reached men at highest risk for syphilis by examining OHTN Cohort Study^a^ subgroup	Increases in screening coverage and frequency (2a&b) occur in the among men at highest risk for syphilis according to sexual behaviors	Outcome measures for screening coverage and screening frequency	GLMM models using SAS PROC GLIMMIX with logit and log link function

*GLMM* general linear mixed models

^a^Ontario HIV Treatment Network Cohort Study, an ongoing clinical HIV cohort taking place at the four participating clinics of the trial [37]. An estimated 40 % of men in HIV care at these clinics are active participants of that cohort

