Despite the guidelines, current levels of screening and testing remain infrequent in many settings [21–23]. Screening is often limited to opportunistic screening when men self-disclose sexual risk behavior. Diagnostic tests are restricted to those presenting with signs or symptoms and miss asymptomatic or mild cases in persons who may not seek medical attention. For example, in a nationally representative sample of persons in HIV care in the USA, only 55 % of sexually active patients were tested for syphilis at least once per year [21]. In Ontario in 2009, 53 % of HIV-positive MSM received syphilis screening or testing on average once per year [22]. As of 2013, we observed only a modest increase in this proportion to 64 % screened annually (unpublished data). Although in Ontario we have observed that HIV-positive men reporting risk behavior are more likely to be tested, there is room for improvement; for example, among men who reported five or more sexual partners in the preceding 3 months, 22 % were not tested for syphilis over the subsequent 2-year period in 2010–2013 [23].

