### Trial aim and objectives

The aim of the ESSAHM trial is to enhance syphilis screening among HIV-positive MSM. We are conducting a clinic-based intervention to incorporate syphilis testing with routine HIV viral load monitoring among HIV-positive men attending four hospital-based HIV outpatient clinics in Toronto and Ottawa, the two largest cities in the province of Ontario. The control condition is the maintenance of current care practices. Specific objectives are to determine to what degree the intervention:Increases the detection rate of untreated syphilis.Increases the proportion of men who undergo syphilis testing at least annually (increased screening coverage)Reduces the interval between syphilis tests (increased screening frequency)Reaches men at highest risk according to sexual behaviors

We hypothesize that the intervention will increase the case detection rate by 75 % or more via an increase in screening coverage to at least 85 % and screening frequency to a median of three tests per person per year. We further hypothesize that increases in screening coverage and frequency will be equivalent among men regardless of sexual behavior characteristics, so that improvements reach men with the highest risk for syphilis infection.

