### Sample size and power

We used two approaches to anticipate power to detect a ≥75 % increase in our primary outcome, the case detection rate based on the effect size reported in pre-/post-intervention studies [24, 26]. First, using a published method for stepped wedge designs [32], we calculated that we could detect a ≥60 % increase in case detection, assuming an overall baseline case detection rate of 2.5 % [14], a sample size of 2278 men from four sites, the stepped wedge design (Fig. 2), 80 % power, a significance level of 0.05, and a within-clinic intraclass correlation coefficient of 0.004 (OHTN Cohort Study, unpublished data). However, that approach assumes independence of observations across time periods [32]. Following a cohort population such as in the ESSAHM trial violates that assumption because the same subject may appear in more than one time period, introducing within-subject correlation [33, 40, 41]. Therefore, we ran extensive simulations to account for within-clinic and within-subject correlation. Under varying assumptions, the simulations demonstrated that a sample size of 2278 men will provide at least 80 % power to detect a ≥75 % increase in the case detection rate (from 2.5 to 4.4 % or higher). Anticipated power is 90 % or greater to detect changes in both secondary outcomes (screening coverage from 55 to 85 %; screening frequency from one test/year to three tests/year).

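### Equivalence of the screening gains across sexual-behaviour groups is to be judged by interaction tests, which cannot show equivalence, and the scale on which the gains should be equivalent is not stated

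*Protocol article*

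**What the plan says.** Under Trial aim and objectives, the hypothesis is that "increases in screening coverage and frequency will be equivalent among men regardless of sexual behavior characteristics"; the reason given is that the improvement should then reach the men at greatest risk. Statistical methods sets the purpose and the tool in one sentence. The purpose is "To determine whether the intervention effects on screening coverage and frequency are equivalent among men across sexual behavior characteristics", and the tool is "we will test for statistical interactions between the fixed effect due to the intervention and sexual behavior variables". Table 1, row 2c, gives the models as "GLMM models using SAS PROC GLIMMIX with logit and log link function", fitted in the OHTN Cohort Study subgroup, estimated at 40 % of the men at these clinics. The same row words the hypothesis differently: "Increases in screening coverage and frequency (2a&b) occur in the among men at highest risk for syphilis according to sexual behaviors".

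Two other statements bear on the point. The Background reports that in Ontario "HIV-positive men reporting risk behavior are more likely to be tested", so the groups are expected to start from different levels. Sample size and power claims 90 % power or more for the secondary outcomes, but only for the overall change ("screening coverage from 55 to 85 %; screening frequency from one test/year to three tests/year"). The article gives no margin, effect scale or power for the comparison between behaviour groups.

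**The concern.** The plan names a conclusion (equivalent effects) and a procedure (an interaction test) that cannot deliver it. If non-significance is read as equivalence, the conclusion becomes easier to reach as the data become fewer, and this analysis uses only a subset of the men.

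The second difficulty is the meaning of equivalent. When groups start from different levels, equal final level, equal absolute gain and equal odds or rate ratio cannot in general hold together. The models test the ratio version, while the hypothesis speaks of increases and the targets are common levels (85 % tested annually, a median of three tests a year). At stake is the fourth trial objective, whether the intervention reaches the highest-risk men. A real shortfall could be reported as equivalence, and full success on the common targets could be reported as a lack of it.

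**Working it through.** **1. The plan's own power figure.** Closed-form stepped-wedge variance with I = 4 clinics, T = 5 six-month periods, n = 2278/4 = 569.5 men per clinic-period, ICC 0.004, mean proportion 0.70 and two-sided 0.05 (sidedness assumed).
- Total variance 0.70 × 0.30 = 0.21; τ² = 0.004 × 0.21 = 0.00084; σ² = 0.996 × 0.21/569.5 = 0.000367. Design constants U = 10, W = 30, V = 30.
- Var = Iσ²(σ² + Tτ²) / [(IU − W)σ² + (U² + ITU − TW − IV)τ²] = 6.71×10⁻⁶ / 0.02887 = 0.000232, so SE = 0.0152.
- z = 0.30/0.0152 ≈ 20, power above 99.9 %.

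This agrees with the stated 90 % or greater. It concerns the overall effect and says nothing about differences between groups.

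**2. How often a real shortfall gives a non-significant interaction.** Inputs from the article: about 3100 men, 40 % in the cohort (1240), coverage 55 % to 85 %, alpha 0.05. Assumed: 60, 150 or 250 high-risk men, both groups starting at 55 %, and one independent control and one independent intervention observation per man.
- Effect: ln(ratio of odds ratios). SE = √Σ 1/[n p(1 − p)] over the four group-by-condition cells.
- Worked case, 150 high-risk and 1090 other men, reaching 80 % and 85 %: ln(4.00/5.67) = −0.348. Variance = 0.00371 + 0.00720 + 0.02694 + 0.04167 = 0.0795, SE = 0.282, z = 1.24, power 23.5 %, missed 76.5 %.

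| High-risk men | 80 % vs 85 %: z, missed | 75 % vs 85 %: z, missed |
|---|---|---|
| 60 | 0.82, 87 % | 1.56, 66 % |
| 150 | 1.24, 77 % | 2.35, 35 % |
| 250 | 1.51, 67 % | 2.86, 18 % |

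If the cohort share is taken of 2278 instead, the subset is about 911 men. Over 911 to 1240 men and a high-risk share of 10-50 %, the missed fractions are about 55-84 % for 5 points and 7-54 % for 10 points.

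**3. Dependence on scale.** Assumed baselines: others 50 %, high-risk 60 %.
- Equal 30-point gains (to 80 % and 90 %): odds ratios 4.0 and 6.0, ratio 1.50.
- Equal final level (both 85 %): odds ratios 5.67 and 3.78, ratio 0.67; gains 35 and 25 points.
- Equal odds ratio 5.67: high-risk odds 1.5 × 5.67 = 8.5, or 89.5 %; gains 35 and 29.5 points.

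The interaction therefore points in opposite directions under the first two readings. With equal baselines of 55 % and a common final 85 %, the ratio is 1.00 and there is nothing to flag.

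Probability of a significant interaction when both groups reach 85 % (1240 men, 150-250 high-risk): 27-38 % from 60 % vs 50 %, and 53-71 % from 65 % vs 50 % (ratio 0.54).

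For frequency, with Poisson counts and both groups reaching three tests a year from 1.0 and 1.5, the rate ratios are 3.0 and 2.0, ratio 0.67, flagged in over 99 %. Equal gains of two tests a year from the same baselines give 3.0 and 2.33, ratio 0.78.

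**4. What an interval approach could deliver.** The 90 % half-width for the difference in absolute increase is 1.645 × √Σ p(1 − p)/n. With both groups going from 55 % to 85 %, it is 13.3, 8.8 and 7.1 points for 60, 150 and 250 high-risk men.

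**The case against.** The strongest reply is that the hypothesis concerns increases. Groups that finish at 85 % from different starting points have unequal increases in percentage points as well as on the odds scale, so a significant interaction there is a correct answer and not an artefact of the link. That stands. A reader might infer that the test would necessarily declare non-equivalence whenever everyone reaches the target. The article does not support this, because a flag needs unequal baselines and enough power, and only the direction of the baseline difference is documented.

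A reader might also take 78 % as the high-risk baseline from the Background's 22 % untested among men with five or more partners. That figure covers two years, while the 85 % target is annual. Annual coverage in those men is at most 78 %, and if testing were independent between years it would be 1 − √0.22 = 53 %. Flag rates built on 78 % should not be used.

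The group sizes are assumed, and the four-cell standard error ignores period, site and within-man correlation. Table 1 also models testing per six-month period, not per year. The percentages above are therefore illustrations and not properties of the planned model.

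Table 1 is a second wording of the hypothesis, in visibly garbled text, and the aims section links the two ideas. Finally, margins are often left to an analysis plan, and this is a secondary question in a subset. Both are true, but the article itself says that the interaction test is how equivalence will be determined, and adding a margin later would mean changing that rule.

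**Conclusion.** The concern holds in two parts. First, the stated rule cannot support the stated conclusion. This does not depend on the assumed inputs; those only set the size, which is about 67-87 % missed for a 5-point shortfall and 18-66 % for a 10-point shortfall under the illustration. Second, equivalence is left without a scale in a setting where the article expects unequal baselines. At baselines such as those illustrated, equal absolute gains and equal final levels both give a non-null ratio-scale interaction, with opposite signs. A flag can therefore arise even when high-risk men reach the common target, but it need not.

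The consequence is limited to the fourth objective. The primary outcome and the overall secondary comparisons are untouched. The point should be corrected, because the remedy needs only wording and output from models already planned.

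**What to change.** - State that a non-significant interaction will not be read as equivalence.
- From the same models, report coverage and tests per year in each behaviour group under control and under intervention, and the between-group difference in the absolute increase, each with a confidence interval.
- Claim equivalence only if the 90 % interval for that difference lies within a margin fixed in advance.
- Report the level reached by the highest-risk men against the 85 % and three-test targets. This is additional: a comparison of final levels alone would not test whether the increases are equivalent, since a group already at target could have gained nothing.
- Keep the interaction as an estimate with its interval.
- Align Trial aim and objectives, Statistical methods and Table 1 row 2c to one hypothesis.

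The cost is protocol and analysis-plan wording plus predicted margins from the fitted models; no new data are needed. The drawback is that an equivalence claim may be out of reach if few men are high-risk. With 60 such men the 90 % half-width is already about 13 points, so a 10-point margin (used here only as an example) could not be met even with identical observed gains. The interval would at least show this openly.

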### Outcomes

The primary outcome is the detection rate of new, previously untreated syphilis cases, specifically acute infectious syphilis. The centralized provincial laboratory in Ontario is the repository of all syphilis tests in Ontario, and these will be accessed to help with syphilis diagnoses. This laboratory uses the following “reverse algorithm” for the serologic diagnosis of syphilis: (1) screen with chemoluminescent (CLIA) test; (2) if CLIA is reactive or indeterminate, additional testing is performed with the rapid plasma reagin (RPR) test as well as the *T. pallidum* particle agglutination (TPPA) test for confirmation of CLIA screening results; (3) if RPR and TPPA are non-reactive or indeterminate, may also include the fluorescent treponemal antibody absorbance (FTA-Abs) test [39]. Based on this approach, a new diagnosis is defined as:Seroconversion with prior negative syphilis serology within the previous 12 months (requires both a reactive syphilis serological screen and a minimum of a second reactive syphilis test using a different serological method, e.g., rapid plasma reagin (RPR)/*T. pallidum* particle agglutination (TPPA); orIn men previously diagnosed with syphilis, a fourfold or greater rise in RPR titre from the last titre within the prior 12 months, indicative of re-infection; orClinical evidence of primary or secondary syphilis together with laboratory confirmation (i.e., direct fluorescent antibody or polymerase chain reaction (PCR) from primary lesions or a positive syphilis screening test together with a second reactive syphilis test using a different serological method).

Diagnoses by clinical (physician ascribed) or laboratory (at least two reactive serological results using different methodologies) criteria which do not meet the above definitions will be considered to be late syphilis (>1 year since infection, non-infectious) or syphilis of unknown duration (if date of infection not known).

Secondary outcomes include screening coverage (proportion of men tested at least once per year) and screening frequency (number of times per year).

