### Timeline

The data collection period will last a total of 30 months. All clinics began with a trial run-in period in November 2014 during which there was no change in current syphilis test ordering practices. The run-in allowed clinics the opportunity to implement and pilot data collection procedures. Feedback during the run-in was used to modify data collection protocols as needed. After the run-in, clinics transitioned into the first official 6-month control period, starting in February 2015, with no change to syphilis testing practices from the status quo. At the end of this period (August 2015), the intervention was implemented at the first clinic as randomly assigned within the stepped wedge (Fig. 1). At the end of each 6-month period, a new clinic will implement the intervention according to their placement on the wedge. By July 2017, all clinics will have implemented the intervention for a minimum of 6 months. Figure 2 outlines the timeline and procedures for data collection.

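### Screening coverage is defined and targeted per year but measured per 6 months and then annualized; the 6-month proportion does not fix the annual one, which dated tests would give directly in three of four clinics

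*Protocol article*

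**What the plan says.** Three places put coverage on an annual scale. The second objective (Trial aim and objectives) is that the intervention "Increases the proportion of men who undergo syphilis testing at least annually". The Outcomes section has "Secondary outcomes include screening coverage (proportion of men tested at least once per year". The hypothesis in Table 1, row 2a (Statistical methods) is "Increase to 85 % of men testing annually".

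The outcome measure in that same row is "Tested one or more times in 6-month study period as a binary measure", analysed by a mixed model with logit link. The methods column adds "Compare proportion tested and modify to annualized rates" and gives no rule. Sample size and power quotes "screening coverage from 55 to 85" % at 90 % power or more, without naming the window.

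Data collection and management says that viral loads and syphilis tests ordered by the clinics are extracted with their dates and results for each 6-month period. Tests ordered by other Ontario providers are extracted by month and year. The Timeline says that by July 2017 "all clinics will have implemented the intervention for a minimum of 6 months".

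**The concern.** The analysed measure is not the defined outcome, and the step between them is a conversion that a proportion does not support. A count rate can be scaled from 6 to 12 months. The proportion of men tested at least once cannot, because the 12-month figure depends on how far the men tested in the first half are the same as those tested in the second. Doubling 70 % would give an impossible 140 %.

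At stake is the reported annual level. The reader will set it against the 85 % target and against the annual figures elsewhere in the article: 53 % and 64 % in the Background, and 43 % of MSM in 2014 under Study setting. A conversion chosen after the data are seen could put the same 6-month result on either side of 85 %. Row 2c reuses the coverage measure for the high-risk subgroup, so the issue carries over there.

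**Working it through.** **1. The plan's own figure.** Sample size and power claims at least 90 % power for coverage from 55 % to 85 %. I used the standard closed form for stepped wedge designs with 4 clinics, 5 six-month periods, 2278/4 = 569.5 men per clinic-period, ICC 0.004 and alpha 0.05 (two-sided assumed). For this layout it reduces to

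Var = 4s²(s² + 5τ²) / (10s² + 30τ²), with s² = p(1−p)/569.5 and τ² = (0.004/0.996)·p(1−p).

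As a check of the layout, the primary outcome (2.5 % to 4.0 %) gives 82 % power with the baseline variance and 72 % with the mean variance, against the stated 80 %. For coverage, with p = 0.55, s² = 0.000435 and τ² = 0.000994, so the standard error is about 0.0166. The difference of 0.30 is about 18 standard errors, and power exceeds 99.9 %. The claim is reproduced.

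If 55 % and 85 % are annual figures, the 6-month contrast is 32.9 % to 61.3 % with independent halves, or 27.5 % to 42.5 % if no man is tested in both. Power exceeds 99.9 % for both. The formula ignores within-subject correlation, but the margin is wide. The choice of scale does not threaten the test.

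**2. From 6 months to 12.** Let p be the 6-month coverage, taken as equal in both halves, and φ the within-man correlation of being tested between halves. Annual coverage is

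A = 1 − [(1−p)² + φ·p(1−p)], with bounds p ≤ A ≤ min(1, 2p).

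At p = 0.70, (1−p)² = 0.09 and p(1−p) = 0.21:

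| φ | Annual coverage at p = 70 % | 6-month p needed for 85 % annually |
|---|---|---|
| 0 (independent) | 91.0 % | 61.3 % |
| 0.2 | 86.8 % | 67.4 % |
| 0.4 | 82.6 % | 73.2 % |
| 0.6 | 78.4 % | 78.2 % |
| 0.8 | 74.2 % | 82.1 % |
| 1 (same men) | 70.0 % | 85.0 % |

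At p = 70 % the 85 % line is crossed where 0.15 = 0.09 + 0.21φ, so φ = 0.06/0.21 ≈ 0.29.

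**3. Where the conversion matters.** If p is 85 % or more, A is at least 85 % whatever the overlap. If p is below 42.5 %, A is below 85 %, since 2p < 85 %. Between these values the answer depends on the overlap.

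**4. What the design lets one observe.** One clinic crosses over every 6 months within 30 months (Timeline):

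| Order on the wedge | Control months | Intervention months | Full 12-month control window | Full 12-month intervention window |
|---|---|---|---|---|
| First | 6 | 24 | no | yes |
| Second | 12 | 18 | yes | yes |
| Third | 18 | 12 | yes | yes |
| Fourth | 24 | 6 | yes | no |

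With dated tests linked to each man, annual coverage can be counted wherever the table says yes. Adding the three-month run-in (November 2014 to February 2015) would bring the first clinic to only nine months of usual care.

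**The case against.** The strongest objection is that the article flags the change of scale openly and that the exact formula belongs in an analysis plan that is not shown. The absence of a formula would indeed be no finding. What remains is that the row fixes an indirect route, from a 6-month proportion to an annual figure, although the same article collects the data for a direct count.

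Several stronger readings are tempting, and the documents do not support them.

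- *The 85 % level cannot be judged.* It can: tests are dated and linked, and 12-month windows under intervention exist in three of four clinics. Only the last clinic's annual intervention coverage and the first clinic's in-trial annual control coverage are unobserved.
- *The intervention contrast is biased, because overlap between halves differs by condition.* Different overlap is plausible, since usual-care testing is prompted by symptoms, exposure or disclosed risk and opt-out testing follows viral loads. No overlap is quantified, however, and nothing says that one conversion serves both conditions. The model is fitted to the unconverted 6-month outcome and is valid for a 6-month effect.
- *The conversion moves the result by at most 24 points.* The gap between 61.3 % and 85 % is a difference on the 6-month scale between two scenarios. It is neither a maximum nor an annual difference.
- *The trial passes or fails at 85 %.* That figure is a hypothesised level and a power input. No formal test against it is stated.

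It is also fair to say that independence is probably an optimistic extreme under intervention. Study setting reports a median of three viral loads a year among MSM, so many men would be tested in both halves. An independence formula would then overstate annual coverage.

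**Conclusion.** The point holds for the annual level of a secondary outcome, and only for that. The defined outcome and its target are annual, the analysed measure is 6-monthly, and the stated annualization cannot bridge the two from the 6-month proportion alone. At p = 70 % the annual figure is 91 %, 82.6 % or 70 % for between-half correlations of 0, 0.4 and 1. Whether 85 % is reached can turn on the conversion for any p between 42.5 % and 85 %. The test of the intervention effect and its power stand.

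The figures assume equal 6-month coverage in both halves and the same men observed throughout the year. The correlations are illustrative, as the documents give none.

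**What to change.** 1. Keep the logit mixed model on the 6-month measure as the test of the effect, and report it as a 6-month effect.
2. In Table 1, row 2a, replace the annualization with a direct count from linked dated tests: the proportion of men tested at least once in a 12-month window lying wholly within one condition. Use the first three clinics under intervention (24, 18 and 12 months) and the last three under control (12, 18 and 24 months).
3. State that the last clinic under intervention and the first clinic under control contribute only to the 6-month measure for that condition. A labelled sensitivity analysis may fill these gaps from pre-trial records or from the between-half overlap estimated in the other clinics. Pre-trial records lie outside the randomised wedge, and the article does not clearly specify exact dates for them.
4. State how men observed for less than 12 months in a condition are handled.
5. State which window the 55 % and 85 % in Sample size and power refer to.

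The cost is wording and some analysis work; follow-up test dates are already collected. The downside is that the annual 85 % level is assessed in three of four clinics, as a descriptive result.
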